## Abstract

**Background:**

Childhood-onset Systemic Lupus Erythematosus (cSLE) is an autoimmune disease associated with fatigue, mood symptoms, and pain. Fortunately, these symptoms are potentially modifiable with psychological intervention such as cognitive-behavioral therapy (CBT). The Treatment and Education Approach for Childhood-onset Lupus (TEACH) program is a CBT intervention developed to target these symptoms for adolescents and young adults with cSLE. This pilot randomized controlled trial (RCT) aims to determine the feasibility and effect of TEACH for youth with cSLE. Adjustments to the study protocol following the COVID-19 pandemic are also described.

**Methods:**

This two-arm multisite RCT will explore the feasibility (primary outcome) and effect (secondary outcome) of a remotely delivered TEACH protocol. Participants will be randomized to a six-week remotely delivered TEACH program plus medical treatment as usual (TAU) or TAU alone. We will include patients ages 12–22 years presenting to rheumatology clinics from six sites. Validated measures of fatigue, depressive symptoms, and pain will be obtained at baseline and approximately eight and 20 weeks later. Protocol adjustments were also made due to the COVID-19 pandemic, in collaboration with the investigative team, which included patients and caregivers.

**Conclusions:**

Findings from this multi-site RCT aim to document the feasibility of TEACH and provide an estimate of effect of a remotely delivered TEACH protocol on fatigue, depression, and pain symptoms in youth with cSLE as compared to standard medical treatment alone. This findings may positively impact clinical care for patients with cSLE. Clinical trials.gov registration: NCT04335643.

## Introduction

Childhood-onset Systemic Lupus Erythematosus (cSLE) is a chronic, multisystem, autoimmune disease disproportionately impacting females of color [1]. Individuals with cSLE often experience fatigue, depressive symptoms, and pain, which negatively impact health-related quality of life [2, 3]*.* One-third of youth with cSLE have a psychological disorder (e.g., depression or anxiety), which is higher than rates observed in the general population [4, 5]. Additionally, anxiety and depression in children with chronic illnesses increased during the COVID-19 pandemic [6].

Cognitive behavioral therapy (CBT) is the gold standard for treatment of fatigue [7], depression [8, 9], and pain [10, 11] in youth [12] and has improved mental health functioning in adults with SLE [13]. Further, CBT is beneficial for children with diabetes [14], juvenile fibromyalgia [15], and inflammatory bowel diseases [16], with improvements in mood symptoms, adjustment, and medication adherence [17]. Therefore, CBT [8–11]) may improve outcomes for youth with cSLE [18].

Our research team developed the Treatment and Education Approach for Childhood-Onset Lupus (TEACH), a tailored CBT for youth with cSLE targeting mood symptoms, fatigue, and pain [18]. TEACH was originally designed as a six-session, in-person individual treatment. Pilot testing at a single site showed TEACH was potentially beneficial; however, only 50% of patients agreed to participate [18]. Furthermore, barriers (e.g., travel to appointments, patient burden) to treatment were reported. This signaled a critical need to partner with patients and families to refine the intervention to increase access to care.

An advisory co-investigative team including five cSLE patients and caregivers collaborated to refine TEACH to be delivered remotely. The team then received funding from the Childhood Arthritis and Rheumatology Research Alliance – Arthritis Foundation (CARRA-AF) to conduct a pilot randomized clinical trial (RCT) to investigate the feasibility of the *remotely delivered* TEACH plus standard medical treatment as usual (TAU) and its effect on fatigue, depressive symptoms, and pain as compared to TAU alone. It is hypothesized that TEACH + TAU will be feasible and more effective at reducing these symptoms compared to TAU alone. This paper details the study protocol and modifications made as a result of the COVID-19 pandemic.

### Study aims and hypotheses

#### Primary outcomes

To determine the feasibility of a remotely-delivered TEACH program for youth with cSLE. Program feasibility will be based on recruitment/retention rates and qualitative participant interviews. It is hypothesized that > 65% of people approached will agree to participate (H1) and > 80% will complete the TEACH protocol (H2). Additionally, it is hypothesized that TEACH participants will support program feasibility through qualitative interviews (H3).

#### Secondary outcomes

To examine the effect of TEACH in youth with cSLE. It is hypothesized that fatigue (H1), depressive symptoms (H2), and pain (H3) will significantly decrease for the TEACH + TAU group at post assessment compared to the TAU group.

#### Exploratory outcomes

Exploratory outcomes include health-related (e.g., disease activity/severity, health-related quality of life, pain interference, medication adherence) and mental health-related (e.g., anxiety, resilience; ACEs; COVID-related participant distress; and caregiver mental health) outcomes will be collected, in addition to daily diaries of fatigue, mood symptoms and pain. Long term outcomes (20 weeks from baseline) will also be explored. The impact of sociodemographic factors on treatment response will also be investigated.

## Methods

### Study design

This two-arm, international multi-site RCT will examine the feasibility and effect of a remotely delivered TEACH protocol in reducing symptoms in youth with cSLE. Six children’s hospitals (five in the United States [US], one in Canada [CAN]) plan to recruit participants. The anticipated participating sites expanded to this total number following the onset of the COVID-19 pandemic. All sites have established pediatric rheumatology programs with a substantial referral base. Two primary locations in the US (Michigan State University [MSU], led by [name]) and CAN (The Hospital for Sick Children, led by [name]) will coordinate study activities. Each primary location houses site PIs, interventionists, and research coordinators. MSU will receive referrals from the US-based sites: Helen DeVos Children’s Hospital, Seattle Children’s Hospital), Montefiore Medical Center/The Children’s Hospital at Montefiore), University of Alabama-Birmingham/Children’s of Alabama), and Cincinnati Children’s Hospital and Medical Center (see Fig. 1).

**Fig. 1 Fig1:**
[figure not shown]
Referral, screening, and enrollment by referral site. Each rheumatology sites’ medical/research team will identify potentially eligible participants. US patients will be referred to research staff at MSU for consenting (if needed), screening, and enrollment. CAN patients will complete these study activities (e.g., consenting, screening, enrollment) with research staff at their home site, Toronto Hospital for Sick Children

Each referring site is anticipated to enroll between 5 and 20 participants, with an anticipated total of 75 participants. Across all sites, we expect a retention rate of 80% and a final sample size of *n* = 60 participants completing the post assessment. A longitudinal design will be employed with assessments at baseline, post-assessment (eight weeks later), and 20-week follow-up from baseline. Feasibility (primary outcome), symptom response (secondary outcome), and additional factors will be assessed at each time point (see below).

### Eligibility criteria

Seventy-five participants ages 12–22 years diagnosed with cSLE from participating rheumatology clinics will be enrolled.

*Inclusion criteria* will include patients who must: be diagnosed with cSLE, meeting the revised American College of Rheumatology Classification Criteria for SLE by age 18 [19]; be between the ages of 12 and 22 years; have clinical elevations in fatigue or depressive symptoms, or pain (see Measures section); have English language proficiency; and those under age 18 must be accompanied by a primary caregiver with English language proficiency willing to participate.

*Exclusion criteria* include patients with: other chronic medical conditions (e.g., juvenile idiopathic arthritis); a documented developmental delay, severe cognitive impairment, thought disorder; or an untreated major psychiatric illness (e.g., bipolar disorder, psychosis, severe depression, or active suicidal ideation (see Measures section)). In cases where patient safety is a concern, study staff will be notified immediately and a risk assessment will be conducted with oversight from a study psychologist. Parents will be informed for youth under 18 years, and appropriate safety measures (e.g., outpatient referrals, hospitalization) will be taken. Of note, the depressive symptom exclusionary criterion was adjusted by the study team given increased depressive symptoms in the cSLE population following the onset of COVID-19 [6]. Specifically, cut-off scores on the depression inventory were adjusted from T-score > 80 to T-score > 90 in August of 2021.

### Study procedures

Physicians will identify youth who meet criteria for cSLE, introduce the study, and then study staff will speak with the family to obtain consent/assent. If study staff are not physically present, virtual consent procedures will be conducted via phone and REDCap’s eConsent Framework to minimize patient risk. After consent, study staff will conduct a psychosocial screening to determine eligibility (~ 5 min), as well as a baseline assessment with qualifying youth (see Fig. 1). Eligible patients will then be randomized to receive TEACH + TAU or TAU alone (See Fig. 2). Approximately eight and 20 weeks later, all subjects will be re-assessed on study outcomes. If significant symptom levels remain (or if family requests additional care), participants will be offered appropriate referrals. Following the post assessment, those randomized to TAU will then be eligible to receive TEACH+TAU (see Fig. 2). Subjects will receive up to $100 in Amazon gift cards ($50 at baseline and $50 at the eight-week assessment; no compensation is offered for 20-week assessment). Participants at the CAN site will receive research volunteer hours at the 20-week visit.

**Fig. 2 Fig2:**
[figure not shown]
Study Design and Timeline. After consenting, participants will be screened for study eligibility. If eligible, participants will complete a baseline assessment and will then be randomized to TEACH + TAU or medical TAU alone. All participants will complete a post assessment approximately eight weeks after baseline. If they were randomized to TAU alone, they will be able to participate in TEACH + TAU after the post assessment is completed. An additional follow-up (20 weeks from baseline) will also be conducted with all participants

### Randomization and blinding

Eligible participants will be randomized to receive either TEACH + TAU or TAU alone in this open trial. Randomization scheduling will be computer-generated by a biostatistician at MSU and stratified based on the two main study sites and two age groups (< 18, 18 +), with a 1:1 ratio for each condition. We will also use blocking to keep the ratio of TEACH + TAU vs. TAU approximately equal throughout the trial. The study team including the site recruiters will be masked to the block size(s). Post assessment and follow up measures will be collected autonomously using online methods, allowing for blinded collection of outcome data irrespective of group assignment.

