### Assessments & outcome measures

Study assessments will occur at baseline, eight weeks, and 20-weeks following the baseline assessment. Psychometrically validated instruments (self-report unless otherwise indicated) sensitive to change in pediatric health studies will be used to explore secondary and additional outcomes (see below). All online assessments will be delivered directly to participants, caregivers, and referring rheumatologists and collected via autonomous self-report in REDCap. The lead research coordinators will oversee data collection to ensure data is complete and collected in a timely manner.

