### Secondary outcomes

#### Fatigue

Fatigue in the past seven days will be measured via the *PROMIS Pediatric Fatigue Short Form* or *Adult Short Form* [20, 21]. Adolescent participants will complete the pediatric short form which includes 10 items scored on a 5-point Likert scale (*0* = *never, 4* = *almost always*) to generate a score 0–40, with higher scores indicating more fatigue. Young adult participants will complete the adult short from that consists of eight items scored on a 5-point Likert scale (*1* = *not at all, 5* = *very much*) to create score 8–40, which are converted into T-scores. T-scores ≥ 60 are eligible.

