## Discussion

cSLE is a chronic, debilitating autoimmune disease associated with more severe symptoms as compared to adult-onset SLE and a 20-fold increased risk of mortality [49]. cSLE is commonly associated with fatigue, mood issues, and pain, which contribute to poor health-related quality of life [2, 3]. Given these common symptoms are modifiable with nonpharmacological therapies, CBT may optimize patient outcomes as part of a multi-disciplinary approach to care [50]; however, there is mixed evidence to date that CBT manages mood and related symptoms in children [18, 51] and adults [13] with SLE. A tailored intervention such as TEACH using evidence-based cognitive behavioral and mindfulness meditation techniques to manage fatigue, depressive symptoms and pain may be needed to address concerns specific to this population.

While we have demonstrated feasibility of TEACH in a pilot investigation [18], a rigorous and well-controlled trial of this promising approach is critically needed to advance understanding and improve outcomes for youth with cSLE. TEACH is a brief tailored therapy designed to improve fatigue, mood, and pain in youth with cSLE. It is important to assess if TEACH is feasible and associated with improvements in these symptoms following treatment as compared to standard medical care. Once these effects are established, we will investigate additional factors such as patterns/predictors of treatment response.

COVID-19 impacted the study planning and recruitment plan. As such, COVID-related distress will now be measured and targeted. Furthermore, we expect enrollment rates to vary during different periods of the COVID-19 pandemic. We will examine these data carefully in the context of when it was collected.

We anticipate minimal risk and maximal benefits to patients/families. The present trial allows for understanding of treatment effects. Lack of active treatment comparator and a modest sample size are limitations. In the future, we plan to test the *implementation* of TEACH in a larger scale multi-site investigation and assess sustainability of treatment effects. Assuming TEACH is effective and future implementation efforts are successful, we will share the program with rheumatology providers to integrate TEACH into routine care. Future work will also examine mechanisms of treatment response and whether modifications (e.g., booster sessions) are needed.

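### Outcome collection is called blinded in an open trial, but participants who know their arm rate all three secondary efficacy outcomes; online completion removes only staff influence

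*Protocol article*

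**What the plan says.** Two statements stand in the same paragraph of the protocol article, under Randomization and blinding. The first sets the design: "Eligible participants will be randomized to receive either TEACH + TAU or TAU alone in this open trial". The last says that the post-assessment and follow-up measures are completed online without staff, "allowing for blinded collection of outcome data irrespective of group assignment".

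Under Assessments & outcome measures, self-report is the default for all instruments, and the online assessments are "collected via autonomous self-report in REDCap". The aims section names the efficacy hypotheses: "It is hypothesized that fatigue (H1), depressive symptoms (H2), and pain (H3) will significantly decrease for the TEACH + TAU group". The Discussion closes its account of weaknesses with "Lack of active treatment comparator and a modest sample size are limitations".

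**The concern.** Whether outcome assessment is blinded depends on whether the person making the rating knows the allocation. For a self-reported symptom that person is the participant. If participants know their arm, an online form does not change what they know; it only takes an interviewer out of the exchange. The paragraph thus attaches the word *blinded* to something narrower.

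This matters because all three efficacy outcomes are subjective. Participants who have had six sessions of attention from a therapist, and who expect to improve, may report fewer symptoms than those still waiting for the programme, even without any specific effect of TEACH. A reader who takes the blinding statement at face value could rate the risk of detection bias as low and read the efficacy result as firmer than the design allows.

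**Working it through.** No figure in the document decides this point, so the check sets the relevant sections side by side.

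**1. Who rates the efficacy outcomes?**
- Fatigue: PROMIS short forms. The Fatigue section says "Adolescent participants will complete the pediatric short form", and young adults complete the adult form.
- Depression: CDI-II or BDI-II. No other rater is named, so the self-report default applies.
- Pain: a 0 to 10 visual analogue scale. Again no other rater is named.

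The participant is the assessor for three of three.

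**2. Does that assessor know the arm?**
- The Intervention section describes six weekly live video sessions in the TEACH arm. The comparison arm has medical care as usual alone (Medical TAU).
- Study procedures and the legend to Fig. 2 say that those allocated to usual care may take up TEACH once the post assessment is done.
- No sham, attention control or masking of participants is described.

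A participant cannot be unaware of which arm this is. The article's own term, *open*, agrees.

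**3. What does online self-completion protect against?**
- Study procedures has study staff carry out the screening and baseline assessment, both before randomisation.
- The blinding sentence concerns only the later measures, which the participant completes alone.
- A staff member who knows the allocation therefore does not put the questions or record the answers. That removes interviewer influence. It does not remove the participant's own knowledge.

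**4. Is the statement corrected elsewhere?**
- The Discussion names the lack of an active comparator and the modest sample size. The first is about what the control arm receives. It is related to attention and expectancy, but it does not say that the raters are aware of their allocation.
- No section lists unblinded self-report as a limitation.

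**5. Which outcomes fall outside the point?**
- Recruitment and retention are counts and do not depend on a symptom rating. The feasibility interviews are conducted by a person, so the sentence about online collection does not describe them.
- SLEDAI-2K and SDI are recorded by study rheumatologists. They are exploratory, and the article does not say whether those raters know the arm. They neither support nor refute the sentence.

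Steps 1 and 2 together contradict the word *blinded* for the efficacy outcomes. Step 3 shows what the sentence can properly claim.

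**The case against.** The best defence is that the sentence speaks of blinded *collection*, not of blinded participants. It comes after an explicit statement that the trial is open, and it is confined to measures taken after allocation. Read that way, it says that no unblinded staff member administers the questionnaires, which is true and worth having. A careful reader also has the means to work out the rest, since the open design, the self-report default and the live sessions are all disclosed. The missing active comparator, which is what leaves attention and expectancy uncontrolled, is already admitted. Finally, self-report by aware participants cannot be avoided when live therapy is compared with usual care, and the affected outcomes are secondary in a pilot whose primary question is feasibility.

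Most of this stands. It shows that nothing is concealed, that online collection has value and that the open design is not itself a fault. It does not rescue the wording. In a section on blinding, a claim of blinded outcome collection will be read as masked outcome assessment, and for these outcomes that is untrue. Nor does admitting the lack of an active comparator tell the reader that the raters knew their arm.

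A reader might go further and infer that the stated protection is empty, or that the protocol claims its participants are blinded. The document supports neither. The protection from staff influence is real, and the paragraph says openly that the trial is not masked.

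**Conclusion.** The sentence is wrong as written and needs correcting, at modest severity. Assessment of fatigue, depression and pain is not blinded; it is free of staff influence only. The conclusion rests on the article's own description of who completes the measures and what each arm receives, plus the ordinary meaning of blinded assessment. It needs no numerical assumption, and no full protocol or analysis plan could make a self-rater who attended the sessions unaware of having done so.

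The reach is three of three secondary efficacy outcomes, together with the exploratory measures that participants rate themselves. The primary recruitment and retention rates are untouched.

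The size of any bias cannot be derived. A reader might want to express it as a share of the planned effect of 0.6. The document gives no bias size, and its Sample Size Estimate does not state the standard deviation behind the 0.6, so any such share would be only an assumption divided by 0.6. Nor does the point show that an observed benefit would be spurious. It limits what a benefit could be attributed to.

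**What to change.** 1. **Randomization and blinding.** Replace the final sentence with wording such as: *Post-assessment and follow-up symptom outcomes are self-reported online by participants who are aware of allocation; staff do not administer them, which limits interviewer influence, but assessment is not blinded.*
2. **Discussion.** Add unblinded self-report of the symptom outcomes to the limitations, next to the lack of an active comparator.
3. **Efficacy conclusion.** Word it as the effect of offering TEACH plus usual care against usual care alone, with attention and expectancy included in that effect.
4. **Optional.** Ask the rheumatologists who score SLEDAI-2K and SDI to remain unaware of the arm, and describe those ratings as masked only if this is achieved. These outcomes are exploratory, so the correction does not depend on it.

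Items 1 to 3 change wording only. No sample size, endpoint, analysis or trial procedure is altered. The price is that the stated rigour reads slightly less favourably.

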### Assessments & outcome measures

Study assessments will occur at baseline, eight weeks, and 20-weeks following the baseline assessment. Psychometrically validated instruments (self-report unless otherwise indicated) sensitive to change in pediatric health studies will be used to explore secondary and additional outcomes (see below). All online assessments will be delivered directly to participants, caregivers, and referring rheumatologists and collected via autonomous self-report in REDCap. The lead research coordinators will oversee data collection to ensure data is complete and collected in a timely manner.

